### Data and safety monitoring

The trial is monitored by a four-person Data Safety Monitoring Board (DSMB). It was mutually determined between DSMB members and study investigators that if the CETA intervention displayed statistically significant effectiveness with at least a moderate effect size at the 12-month follow-up assessment, it would be ethically appropriate to stop the trial and offer the intervention to control participants. Therefore, the DSMB will conduct an effectiveness analysis following the completion of the 12-month post-baseline assessments. The trial will be unmasked and stopped if there is a statistically significant difference between the change in primary outcome (i.e. SVAWS score among female participants) by treatment arm, defined as a Cohen's *d* effect size of ⩾0.5 and a *p* value of <0.05. In that scenario, control participants would not be assessed at 24 months post-baseline but would be offered CETA, and CETA participants would still be assessed at 24 months as planned to measure whether treatment effects were sustained. If no significant difference in change in SVAWS score by treatment arm is found in the 12-month DSMB analysis, the trial will continue as planned with all participants assessed at the primary study endpoint of 24 months (see Fig. 1).

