**Methods/design:**

Study participants are families consisting of three persons: an adult woman, her male husband or partner, and one of her children aged 8–17 (if available). Eligibility criteria include experience of moderate-to-severe intimate partner violence by the woman and hazardous alcohol use by her male partner. Family units are randomized to receive CETA or treatment as usual. The primary outcome is VAWG as measured by the Severity of Violence Against Women Scale, assessed along with secondary outcomes at 24 months post-baseline. Interim assessments are also conducted at 4–5 months (following CETA completion) and 12 months post-baseline.

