### Data analysis

Sample size calculations were informed by a study conducted in South Africa that used the SVAWS physical violence subscale to measure violence among women who had been abused by a partner with an alcohol use problem (Peltzer & Pengpid, 2013). We calculated the sample size needed to obtain a 20% reduction in SVAWS physical violence subscale score among intervention participants at a 24-month follow-up, assuming no change among control participants, using a two-sample independent means *t* test. For 80% power at an *α* level of 0.05, we calculated that we would need to enroll a minimum of 50 families in each study arm to detect this difference in change in means, which we inflated to 84 per arm to account for loss to follow-up and the possibility of small clustering effects at the provider level.

All primary analyses will be based on an intent-to-treat approach with all participants who were randomized included in the final analysis. Loss to follow-up and missing data will be addressed by using multiple imputation (Azur *et al.*
2011). We will estimate linear (continuous outcomes) and generalized linear (binary outcomes) mixed-effects models that will incorporate a random intercept term to account for within-subject correlation on repeated measures. The outcome scores at the three follow-up times will be modeled separately using treatment arm, baseline symptom score (if there is a meaningful difference between the study arms at baseline), time, and an interaction between each treatment arm and time as fixed covariates in each model.

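### If the 12-month rule stops the trial, the 24-month primary comparison cannot be made, no replacement is named, and the CETA-only follow-up cannot show a sustained treatment effect

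*Protocol article*

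**What the plan says.** The abstract (Methods/design) gives violence on the SVAWS as the primary outcome, "assessed along with secondary outcomes at 24 months post-baseline". The Data analysis section sizes the trial for a "20% reduction in SVAWS physical violence subscale score among intervention participants at a 24-month follow-up". That calculation takes scores in the control arm to stay where they are. Neither statement depends on the interim result.

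Under Data and safety monitoring, the DSMB analyses effectiveness once the 12-month visits are complete. The trial stops if the arms differ in SVAWS change, "defined as a Cohen's *d* effect size of ⩾0.5 and a *p* value of <0.05". On a stop, "CETA participants would still be assessed at 24 months as planned to measure whether treatment effects were sustained". For the other arm, the article says that "control participants would not be assessed at 24 months post-baseline but would be offered CETA". If no significant difference is found, "the trial will continue as planned with all participants assessed at the primary study endpoint of 24 months".

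On the analysis set, Data analysis says: "All primary analyses will be based on an intent-to-treat approach with all participants who were randomized included in the final analysis". Multiple imputation is planned for loss to follow-up and missing data. The models carry arm, time and arm-by-time terms over the three follow-up times.

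**The concern.** The two parts of the article do not fit together in the stop branch. The primary time point is 24 months, but that branch removes every later control assessment and gives controls access to the intervention. Nothing moves the primary analysis to 12 months. If the choice is left until the 12-month result is known, the primary time point will have been picked after seeing a positive finding.

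The stated purpose of the remaining 24-month visit is also wrong. A treatment effect is a difference between randomised arms, and a visit attended by one arm does not contain one. At stake is a durability claim about reducing violence that would rest on an uncontrolled series while being described as a sustained effect.

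**Working it through.** **Inputs**
- 50 families per arm, 80% power, alpha 0.05, inflated to 84 (Data analysis). Sidedness is not stated; two-sided is assumed.
- 248 families, 1:1, so about 124 women per arm; loss of up to 30% (Modification to study protocol). 124 × 0.70 = 86.8, taken as 87.
- Stop rule: observed d of at least 0.5 with p below 0.05 (Data and safety monitoring).
- Baseline SVAWS physical violence mean 60.7, SD 16.8 (Table 3); entry at a score of 38 or more (Eligibility screening).
- Visit dates (Trial status).

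**1. The plan's own figures.** The total reproduces: 2 × 84 + 80 = 248. The 50 per arm cannot be checked, because the mean and SD from the South African study are not given. It can be inverted: d = (1.960 + 0.842) × √(2/50) = 0.56. For context, 20% of the trial's own baseline mean is 12.14, and 12.14/16.8 = 0.72. That does not show 50 to be wrong, since it uses different inputs.

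**2. What is left at 24 months after a stop.** Second-cohort 12-month visits fall in November and December 2017. First-cohort 24-month visits begin in May 2018. A stop acted on in that gap leaves no control woman with a 24-month score. The 24-month arm difference and the 24-month arm-by-time term then have no data on one side.

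**3. How likely the branch is.** The smallest significant d is t(0.975) × √(2/n): 0.299 with 87 per arm and 0.250 with 124. The requirement of d at least 0.5 is therefore the binding one. P(stop) is the probability that a noncentral t, with 2n − 2 degrees of freedom and noncentrality d√(n/2), exceeds 0.5√(n/2).

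| True d at 12 months | 87 per arm | 124 per arm |
|---|---|---|
| 0.40 | 26% | 22% |
| 0.50 | 50% | 50% |
| 0.56 | 65% | 68% |
| 0.72 | 93% | 96% |

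**4. What one arm can show.** Change in the CETA arm = effect of CETA + change that would have occurred without it. With no controls the two terms cannot be separated. On the baseline SD, an untreated fall of 3, 6 or 9 points would look like d = 3/16.8 = 0.18, 6/16.8 = 0.36 or 9/16.8 = 0.54. These falls are illustrations; the article gives no figure for untreated change. The one-arm reading equals the effect only if controls would not have changed, which the sample-size section assumes.

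**5. The 12-month estimate, given a stop.** By normal approximation, E[d | stop] = d + SE × φ(a)/P(stop), with SE = √(2/n) and a = (0.5 − d)/SE. For d = 0.56 and n = 87: SE = 0.152, a = −0.40, φ(a) = 0.369, P = 0.655. This gives 0.560 + 0.152 × 0.369/0.655 = 0.646, about 15% too large. The same formula gives about 12% with 124 per arm, 2–3% at a true d of 0.72, and 43–48% at a true d of 0.40.

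**The case against.** The strongest reply is that the article is open about what a stop entails. The phrase calling 24 months the primary study endpoint stands in the branch where the trial continues. The DSMB and investigators agreed on ethical grounds to offer CETA to controls. The stop is triggered by a randomised comparison of the primary outcome after all 12-month visits, so a valid between-arm result exists. Detail on early stopping may also sit in an analysis plan or DSMB charter that is not shown.

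Much of this stands, and it limits the point. Four stronger readings might be inferred, and the document does not support them:
- **That a stop leaves the trial without a result.** It does not; the 12-month randomised contrast remains. It is simply not named as primary.
- **That the plan would impute a whole control arm.** Imputation is planned for loss to follow-up and missing data. Nowhere does the article say it would cover visits cancelled by design.
- **That regression to the mean undoes the 24-month reading.** Selection was at baseline and the SVAWS asks about the past year (Table 2), so by 12 months most of that regression should already have occurred, in both arms. It bears mainly on change from baseline. Other time trends can still affect a one-arm change from 12 to 24 months.
- **That the reported effect would be inflated by nearly half.** That needs a true d of 0.40, where a stop is least likely of the positive effects tabulated. At effects in line with the design, the excess is 12–15% or less.

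The reply does not remove two things. The abstract and the sample-size statement fix 24 months without condition, and the purpose given for the CETA-only visit is an explicit statement, not a gap left to another document.

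**Conclusion.** The point holds as a conflict between stated parts of the article and as a misdescribed purpose for the CETA-only visit. Followed as written, a stop gives a primary time point at which no arm comparison can be estimated and a durability claim without a comparator. The chance of reaching that branch is about 65–68% at the design-implied d of 0.56. This assumes that the effect is already present at 12 months, that the test is two-sided, that there are 87 to 124 women per arm, and that provider clustering is ignored. At a true d of 0.40 it is 22–26%. The absence of 24-month control data assumes the stop is acted on before May 2018. The decision to allow a stop and to offer CETA to controls is not in question. This should be settled before the 12-month analysis, but it does not threaten the 12-month comparison.

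**What to change.** Before the 12-month analysis, add to the protocol and the DSMB charter that, if the rule is met:
1. the intent-to-treat difference between arms in SVAWS at 12 months is the primary analysis;
2. no 24-month comparison between arms is made, and 24-month control outcomes are not imputed;
3. 24-month CETA data are reported as within-arm maintenance from 12 months, and not as a sustained treatment effect.

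Optionally, note beside the 12-month estimate that, given a stop, it is expected to be somewhat too large. A selection-adjusted estimate is not required.

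The cost is wording only, with no new visits or data. The downside is a smaller claim about durability in the stopped scenario.

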### Data analysis

Sample size calculations were informed by a study conducted in South Africa that used the SVAWS physical violence subscale to measure violence among women who had been abused by a partner with an alcohol use problem (Peltzer & Pengpid, 2013). We calculated the sample size needed to obtain a 20% reduction in SVAWS physical violence subscale score among intervention participants at a 24-month follow-up, assuming no change among control participants, using a two-sample independent means *t* test. For 80% power at an *α* level of 0.05, we calculated that we would need to enroll a minimum of 50 families in each study arm to detect this difference in change in means, which we inflated to 84 per arm to account for loss to follow-up and the possibility of small clustering effects at the provider level.

All primary analyses will be based on an intent-to-treat approach with all participants who were randomized included in the final analysis. Loss to follow-up and missing data will be addressed by using multiple imputation (Azur *et al.*
2011). We will estimate linear (continuous outcomes) and generalized linear (binary outcomes) mixed-effects models that will incorporate a random intercept term to account for within-subject correlation on repeated measures. The outcome scores at the three follow-up times will be modeled separately using treatment arm, baseline symptom score (if there is a meaningful difference between the study arms at baseline), time, and an interaction between each treatment arm and time as fixed covariates in each model.

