For this study, CETA was originally planned and initially implemented as a group treatment. Groups were set up to be specific to one participant type (i.e. men, women, or children) and composed of 5–7 individuals. Group assignment was based on the participants’ language, residence, and age (for youth groups). Each group was run by two trained providers pre-paired based on language fluency and location. Specifically, counselors were not allowed to work in or near the neighborhoods where they reside to reduce counselor bias and ensure client anonymity. Groups were designed to run for 90–120 min, with each session beginning with a tea time where participants could socialize to promote group cohesion and motivate regular and punctual attendance. Delivery of CETA included varying elements and ‘dose’ of elements (i.e. the number of sessions or time spent on it) depending on clients’ symptoms, with a suggested 6–12 weekly sessions depending on need. Figure 2 shows a common flow for the men's, women's, and children's group with comments on what might be added for flexibility based on need.

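### The sample size allows for clustering by CETA provider, but the stated model does not; if outcomes correlate within provider, the primary standard error would be too small

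*Protocol article*

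**What the plan says.** All of the following is in the protocol article.

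- **Data analysis, sample size.** The target is "a 20% reduction in SVAWS physical violence subscale score among intervention participants at a 24-month follow-up, assuming no change among control participants", planned "using a two-sample independent means *t* test". This gave 50 families per arm, then "inflated to 84 per arm to account for loss to follow-up and the possibility of small clustering effects at the provider level". The split between loss and clustering, the ICC and the cluster size are not given.
- **Data analysis, model.** The mixed models will "incorporate a random intercept term to account for within-subject correlation on repeated measures". The fixed effects are arm, time, their interaction, and the baseline score if the arms differ meaningfully at baseline. No provider or group term and no cluster-robust variance is named here or elsewhere in the article.
- **CETA.** Sixty-three lay counselors were trained, 43 of them women. Delivery began in groups: "Groups were set up to be specific to one participant type (i.e. men, women, or children) and composed of 5–7 individuals". Two providers ran each group. Counselors choose elements, order and dose according to the client's presentation.
- **Treatment as usual.** The control arm has no study provider.
- **Modification to study protocol after initiation of the trial.** Delivery changed to individual sessions after the first few weeks. Of 83 first-cohort CETA families, 40 women had no group session. A second cohort of 80 families was randomized 1:1, and its CETA families all receive individual delivery. Those who had started in groups could switch or stay.

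**The concern.** The two paragraphs of the Data analysis section do not match. The first treats dependence between women who share a provider as plausible enough to need more families. The second names a variance structure that treats women as independent of one another.

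Some correlation is plausible from the article itself: counselors have latitude over what they deliver, and groups were formed by language and residence. Because this source of dependence exists in one arm only, leaving it out would understate the variance of the CETA mean. The confidence interval for the primary SVAWS comparison would be too narrow and its p value too small, which favours declaring CETA effective.

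**Working it through.** **1. The plan's own figures.** The 50 per arm cannot be reproduced, because the planning mean and SD are not given. At 80% power and two-sided 0.05 (sidedness assumed) it implies a standardized difference of 0.566. As a cross-check only, the baseline table (mean 60.7, SD 16.8) gives a difference of 0.20 × 60.7 = 12.14 and about 31 per arm. Fifty would need an SD of about 21.5. This shows no error. The inflation factor is 84/50 = 1.68. If loss were 30%, 84 × 0.70/50 = 1.18 would remain for clustering; at 20% loss it would be 1.34. The plan therefore has room for a clustering allowance, but its size is not fixed.

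**2. Cluster size.** CETA women: 83 + about 40 = about 123.
- Per counselor: 123/63 = 2.0.
- Per female counselor: 123/43 = 2.9.
- Per provider pair: 123/31.5 = 3.9.

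So m is about 2 to 4. For women treated in groups, m is about 6. At most 83 − 40 = 43 women, or 43/123 = 35%, had a group session.

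**3. Formulas.** With clustering in the CETA arm only and equal arms:
- design effect in CETA: DE = 1 + (m − 1) × ICC
- true SE / model SE: R = √((1 + DE)/2)
- actual type I error: 2 × (1 − Φ(1.96/R))

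Example with m = 4 and ICC 0.05: DE = 1.15 and R = √(2.15/2) = 1.037. The SE is 1 − 1/1.037 = 3.6% too small, and type I error is 5.9%.

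**4. Results.** Every ICC is an assumption.

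| m | ICC | R | SE too small by | Type I error |
|---|---|---|---|---|
| any | 0 | 1.000 | 0% | 5.0% |
| 2 | 0.02 | 1.005 | 0.5% | 5.1% |
| 4 | 0.02 | 1.015 | 1.5% | 5.3% |
| 2 | 0.05 | 1.012 | 1.2% | 5.3% |
| 4 | 0.05 | 1.037 | 3.6% | 5.9% |
| 2 | 0.10 | 1.025 | 2.4% | 5.6% |
| 4 | 0.10 | 1.072 | 6.7% | 6.8% |
| 6 | 0.05 | 1.061 | 5.7% | 6.5% |
| 6 | 0.10 | 1.118 | 10.6% | 8.0% |

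The rows for m = 6 treat every CETA woman as group-treated, so they are an upper end for this trial.

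**5. Simulation check.** Twenty thousand runs per cell, 124 per arm, one time point, no provider term in the test. At ICC 0.05: 5.3% (m = 2), 5.9% (m = 4), 6.4% (m = 6). At ICC 0.10: 5.9%, 6.9%, 8.0%. These agree with the formula to within 0.4 percentage points.

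**6. Cost in power.** The final 248 families are 124 per arm, or about 87 after 30% loss. At the implied difference of 0.566, power is 96% with no clustering and 94% with m = 4 and ICC 0.10.

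**The case against.** **The plan speaks only of a possibility of small effects.** This stands. At an ICC of zero the stated model is right, and with 2 to 4 women per counselor and a small ICC the understatement is minor. A reader might infer that the standard error is certainly too small; the documents give no ICC and do not support that.

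**The implied allowance of 1.18 might seem to measure the error.** A reader might apply it to both arms. That does not hold. The 30% loss is stated for the later sample increase, not for the step from 50 to 84, and the control arm has no providers. In the CETA arm only, 1.18 gives R = √(2.18/2) = 1.04 and type I error of about 6.0%.

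**The 12-month stopping analysis might seem to be compromised too.** The Data and safety monitoring section names no model for that p value, and stopping also needs an effect size of at least 0.5. With about 87 per arm, 0.5 corresponds to t = 0.5 × √(87/2) = 3.30. Divided by the largest R in the table, it is still 3.30/1.118 = 2.95. The effect-size threshold governs the decision, so the point does not extend there.

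**Groups of six do not describe most of the trial.** This stands: at least 80 of about 123 CETA women had no group session.

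**An analysis plan not shown may add a provider term.** It may. But the article does not leave the random structure open: it names one term and its purpose, against a premise stated one paragraph earlier. This limits the severity and does not remove the mismatch.

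**The model also omits compound, a stratification factor.** If compounds differ in outcome, that makes the standard error somewhat conservative. The size is unknown, and the plan gives no ground for relying on it as an offset.

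**Conclusion.** The point holds in conditional form. The plan foresees provider clustering when it sets the sample size and omits it from the stated model. If outcomes correlate positively within CETA provider or group, the primary standard error is understated in CETA's favour. The likely size is modest: type I error of about 5.3 to 5.9% at an ICC of 0.05 and about 5.6 to 6.8% at 0.10, with roughly 2 to 4 women per provider. It would reach about 6.5 to 8.0% only if CETA women were treated in groups of about six.

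These figures assume clustering in the CETA arm only, equal cluster sizes, no loss and a single time point. Loss would shrink the clusters, and unequal caseloads would work the other way. The matter should be put right before the final analysis, but it does not threaten the trial.

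**What to change.** Record the CETA provider, or the provider pair or group, for each woman, and carry that identifier into the analysis file. State in the primary analysis one of the following:

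- a random effect for provider or group in the CETA arm only, with control families as singletons; or
- cluster-robust standard errors with a small-sample correction.

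The second may be the more practical. With about two women per counselor a provider variance is weakly identified, and membership is not cleanly nested because groups had two providers and some participants changed delivery mode. Add a rule, fixed before the primary analysis, for assigning women who moved from group to individual delivery.

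The cost is a few lines of analysis wording and one identifier. Intervals become slightly wider, which the sample size already allows for. Nothing changes for participants.

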## Methods/design

### Overview of study design

The Violence and Alcohol Treatment (VATU) study (*vatu* means ‘ours’ in Nyanja, a commonly spoken language in Zambia) is a parallel group randomized clinical trial comparing the effectiveness of CETA to treatment as usual (TAU) among family ‘units’ consisting of three individuals: an adult woman, her male husband or partner, and one of her children (male or female, ages 8–17). The study settings are three high-density, low-resource ‘compounds’ (i.e. neighborhoods) in Lusaka. Eligible families are randomized as a unit to CETA or to TAU. All participants are assessed at four time points: (1) baseline; (2) 4–5 months (following CETA completion); (3) 12 months; and (4) 24 months post-baseline. The study flow is illustrated in Fig. 1.

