### Assessment of outcomes and follow-up

Post-assessments were conducted with participants starting in October 2016 and are ongoing. All post-assessments (4/5, 12, and 24 months post-baseline) are conducted in the same format (i.e. ACASI), and at the same locations as baseline. At baseline and all follow-up visits, participants are provided with reimbursement for travel. The primary outcome in the study is violence as measured by the SVAWS. Secondary outcomes include alcohol and other SU, mental health, psychological violence, and gender norms. Each participant type (woman, man, child) completes a specific battery of instruments via ACASI. The measures included in ACASI were pilot tested with participants sampled from the same source population as those in the trial to check translation accuracy and item comprehension. In addition to the self-report measures administered via ACASI, a hair sample is collected from participants as a biomarker of chronic stress (Russell *et al.*
2012). The full list of outcome instruments is displayed in Table 2.

**Table 2. tab02:** Primary and secondary outcome measures for VATU trial

				Cronbach's *α*^a^		
Measure	Construct	Reference	Description	Woman	Man	Child
Primary outcome						
Severity of Violence against Women Scale (SVAWS)	Violence	Marshall (1992)	46 items assessing how often (never, once, a few times, many times) a current partner perpetrated acts of violence against the participant in the past year. Subscales include: (a) threats of violence; (b) physical violence; and (c) sexual violence. Previously used in a study of IPV among women with partners who have alcohol abuse in South Africa (Peltzer & Pengpid, 2013)	0.95	–	–
Secondary outcomes						
World Health Organization IPV measure (WHO-IPV)^b^	Violence	World Health Organization (2005)	Nine items assessing how many times a current or previous partner ever and recently perpetrated acts of violence (never, once, a few, many). Previously used in the WHO multi-country study on Women's Health, including in Tanzania and Namibia	0.95	0.96	–
Youth Victimization Scale (YVS)	Violence	Nadel *et al*. (1996)	135 items assessing how often (never, once, sometimes, often) youth have experienced various types of recent violence at school, in the neighborhood, and at home	–	–	0.98

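### A random intercept alone assumes equal variance and correlation across visits; past-year recall makes equal correlation unlikely, so a joint model's 24-month standard error may be wrong, by an unknown amount and in either direction

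*Protocol article*

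**What the plan says.** Under Data analysis, linear mixed models for continuous outcomes will "incorporate a random intercept term to account for within-subject correlation on repeated measures". The next sentence reads: "The outcome scores at the three follow-up times will be modeled separately using treatment arm, baseline symptom score". The baseline score enters only "if there is a meaningful difference between the study arms at baseline". Time and arm-by-time are also fixed effects. No residual structure, visit-specific variance or robust standard error is mentioned.

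Table 2, under Assessment of outcomes and follow-up, describes the primary instrument, SVAWS, as asking how often "a current partner perpetrated acts of violence against the participant in the past year". The Overview of study design sets the schedule: "All participants are assessed at four time points: (1) baseline; (2) 4–5 months (following CETA completion); (3) 12 months; and (4) 24 months post-baseline". Data and safety monitoring names the "primary study endpoint of 24 months".

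**The concern.** A random intercept with independent, equal-variance residuals is compound symmetry: every visit has the same variance and every pair of visits the same correlation. The recall period and the visit schedule do not fit that pattern. Some pairs of visits ask partly about the same months and others share none, and the primary visit is the one that overlaps with nothing.

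If all visits go into one model, the 24-month contrast takes its standard error from variances and covariances averaged over visits. Where the average differs from the 24-month value, the confidence interval and p value of the primary comparison are miscalibrated. Too small a standard error raises the type I error; too large a one costs power.

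**Working it through.** **Inputs from the article.** Recall 12 months; visits at 0, 4–5 (taken as 4.5), 12 and 24 months; 1:1 allocation; 248 families. The only SVAWS SD given is the baseline physical-subscale value, 16.8 (Table 3). No follow-up SD, between-visit correlation or standard error is stated, so the article has no figure of its own to reproduce here. The sample size does not depend on this point.

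**Recall overlap.** Shared fraction = max(0, 12 − gap)/12.
- Baseline with 4.5 months: 7.5/12 = 0.625.
- 4.5 with 12 months: 4.5/12 = 0.375.
- The other four pairs, including every pair with 24 months: 0.

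**Assumed correlation.** Stable between-woman share a, overlap share b and measurement-error share m, with a + b + m = 1. The correlation of two visits is a + b × overlap. SDs are equal and data complete. I compare the random-intercept model's SE with the true SE for the 24-month contrast.

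*(a) One model per follow-up, baseline and 24 months as two rows, difference in change.* There is a single pair, so the average covariance is the true one. Ratio 1.00 under any covariance.

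*(b) Three follow-ups jointly, no baseline term.* The model variance is the mean of the visit variances. With equal SDs the ratio is 1.00, whatever the correlations.

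*(c) Four waves jointly, change from baseline to 24 months.* The model uses the average of six correlations; the truth uses the baseline–24-month one, a. The average overlap is (0.625 + 0.375)/6 = 1/6, so ratio = √[1 − b/(6(1 − a))].
- m = 0: b = 1 − a, so √(5/6) = 0.913 for any a (8.7% too small).
- a = 0.4, m = 0.2: √(1 − 0.4/3.6) = 0.943 (5.7%).
- a = 0.4, m = 0.3: √(1 − 0.3/3.6) = 0.957 (4.3%).
- A larger stable share with measurement error shrinks it further: a = 0.6, m = 0.3 gives √(1 − 0.1/2.4) = 0.979.

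*(d) Three follow-ups jointly with one common baseline slope.* With a = 0.4, m = 0, the correlations with baseline are 0.775, 0.4 and 0.4, and the slope is their mean, 0.525. The residual variance at a visit is 1 − 2(0.525)r + 0.525², giving 0.462, 0.856 and 0.856, mean 0.724. Ratio √(0.724/0.856) = 0.92. With m = 0.2 it is 0.95. Simulation (124 per arm, 3,000 runs) gave 0.928 and 0.949.

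**Adding serial decay (an assumption).** Correlation 0.3 + 0.7 × 0.94^months, reading (c): the average correlation is 0.634 and the baseline–24-month one 0.459. Ratio √(0.366/0.541) = 0.82. Reading (d) gives 0.85. With 20% measurement error the ratios are about 0.88–0.89 in (c) and 0.90–0.91 in (d). The 0.82 is not a ceiling: a decay of 0.97 per month gives 0.78 in (c).

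**Changing the SD (an assumption; correlation 0.5, baseline SD 1.0).** Reading (b):
- SD 1.0/1.2/1.5: √[((1 + 1.44 + 2.25)/3)/2.25] = 0.83.
- SD 1.0/0.9/0.8: √[((1 + 0.81 + 0.64)/3)/0.64] = 1.13, i.e. 13% too large. Reading (c) on the same falling SDs gives 1.02.

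**Type I error implied**, from 2[1 − Φ(1.96 × ratio)]: ratio 0.943, 6.5%; 0.913, 7.4%; 0.90, 7.8%; 0.82, 10.8%; 1.13, 2.7%.

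**The case against.** The strongest objection is that the text says the three follow-up times are modelled separately. If that means baseline plus one visit per model, the standard error is exact and the point disappears. This cannot be excluded, but it fits the rest of the sentence poorly. With one follow-up row per woman, neither time, arm-by-time nor a random intercept can be estimated, and the rescue requires baseline to be an outcome row although it is listed as a covariate. One joint model per outcome is the more natural reading.

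Second, baseline adjustment is conditional. Without it, a joint three-visit model with equal SDs also gives a correct standard error. This stands, and it is why the range starts at zero.

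Third, an analysis plan not shown might set another residual structure or robust errors. That is possible. The article nevertheless makes a covariance choice, and the choice can be judged as stated.

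A reader might go further and infer that past-year recall breaks equal variance by construction, and that the 24-month standard error is therefore 10–18% too small. The article does not support either step. Every recall window is 12 months long, so overlap changes correlations, not marginal variances. The entry threshold of 38 on the physical subscale could compress the early spread, but scores falling toward the floor could compress the late spread, and no follow-up SD is given to decide between them. Overlap alone reaches about 9%; anything larger needs decay or a rising SD that the article does not state.

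**Conclusion.** The point holds as a weakness of the stated method, not as a demonstrated error in the result. If the visits are fitted together, equal correlation is implausible, and the random intercept can misstate the precision of the primary 24-month comparison.

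The size ranges from none, under the two readings above, through about 4–9% too small from overlap alone (stable share 0.4 and up to 30% measurement error; less with a larger stable share), to about 18% too small in the decay and rising-SD cases worked here. With a falling SD the error reverses in most fits. These figures assume complete data within each analysed data set; the planned multiple imputation was not modelled. Neither direction nor size can be settled from the article, which argues for a covariance that does not require guessing.

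**What to change.** State that the three follow-up SVAWS scores are fitted in one model per outcome, with arm, visit, arm-by-visit, baseline SVAWS and baseline-by-visit as fixed effects, and an unstructured within-woman covariance with visit-specific variances. Take the 24-month arm difference from that model. Name the fallback structure to be used if it does not converge, and keep the random-intercept model as a sensitivity analysis. The same sentence should settle what modelling the follow-ups separately means.

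The cost is one or two sentences. Unstructured covariance for three visits has six parameters (three variances, three covariances) against two for the random intercept, which 248 women can support. The small downside is a possible convergence failure, hence the fallback.
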